## Abstract

**Background:**

Globally, tuberculosis (TB) programs have enhanced efforts to improve case detection, treatment initiation, and monitoring of treatment outcomes. However, less attention has been given to reducing the number of persons with presumed TB who never get tested for TB or those with confirmed TB who never start treatment in endemic regions such as Uganda. Such losses hinder progress toward attaining the 2035 End TB goals. The World Health Organization recommends mobile health (mHealth) interventions such as SMS reminders, telephone calls, mobile apps, and digital monitoring devices to foster universal health coverage. To our knowledge, there is limited evidence on whether these mHealth interventions can increase linkage to care for persons with presumed TB, particularly in sub-Saharan Africa.

**Objective:**

We aim to conduct a randomized controlled trial (MILEAGE4TB) whose aim is to assess the effect of SMS reminders, telephone calls, and transport incentives on improving completion of TB diagnosis among persons with presumed TB and initiation of treatment for diagnosed patients in Uganda.

**Methods:**

This will be a 5-arm individual randomized controlled trial among persons with presumed TB aged 18 years or older who are referred for Xpert MTB/RIF testing. Participants will be randomly assigned (2:2:2:1:1) to (1) standard of care, (2) SMS reminders only, (3) telephone calls only, (4) SMS reminders and a transport incentive, and (5) telephone calls and a transport incentive. An estimated sample size of 2389 participants will be considered. The primary outcome will be completion of TB diagnosis, defined as submitting a sputum sample for Xpert MTB/RIF testing and receiving test results within 30 days of being identified as having presumptive TB. The secondary outcomes will include (1) TB treatment initiation, which will be defined as starting TB treatment within 30 days of being diagnosed; (2) median turnaround times for TB diagnosis and treatment initiation; and (3) acceptability and feasibility of the interventions. Participants will be followed for 30 days to check whether they have tested for TB and collected their results. Chi-square tests will be performed for categorical outcomes. Analysis will be by intention to treat. Modified Poisson regression models will be used to estimate the effects of the interventions on completion of TB diagnosis and treatment initiation.

**Results:**

The study was funded in June 2020 and data collection for the trial started in August 2023. Results from this trial are not yet available. As of August 28, 2025, a total of 2355 participants had been recruited. Data from the preliminary analysis will be ready by December 2025 after all trial activities.

**Conclusions:**

This randomized controlled trial will provide insights on the use of mHealth interventions to improve the completion of TB diagnosis among persons with presumed TB and initiation of treatment for diagnosed patients.

## Introduction

### Background

Tuberculosis (TB) remains one of the leading causes of death from a single infectious agent despite the fact that it is preventable [1]. The End TB Strategy of the World Health Organization (WHO) calls for reduction of TB incidence by 90%, deaths by 95% and eliminating catastrophic costs for TB-affected households by 2035; however, progress is hindered by the loss to follow-up (LTFU) of patients along the continuum of care [2]. Patient LTFU can occur after they are identified with presumptive TB but are never tested, while those who are tested and are confirmed to have TB can also undergo LTFU and never initiate TB treatment. This is in addition to the number of patients who never access a TB diagnostic test [3]. In 2023, an estimated 10.84 million people fell ill with TB, of whom 8.16 million were diagnosed and notified to national TB programs, leaving out 2.7 million patients (25%) [1]. A study by Kim et al [4] on TB care cascades of 30 high TB burden countries found that 35% of people with TB did not receive a diagnosis, while 5% of people who were diagnosed did not initiate treatment.

The WHO recommends the use of mobile health (mHealth) for improved service delivery and continuation of health care, given its timeliness, popularity, and affordability [2,5]. SMS reminders, telephone calls, and mobile apps are some of the interventions being used to support TB care and reduce patient LTFU during the treatment phase [6-10]. These mHealth interventions have shown promise in improving adherence to TB treatment in previous studies [11-14]; therefore, they have the potential to also support persons with presumed TB to complete the diagnostic process. Incentives given to patients have also been found to improve health care outcomes elsewhere [15-19]. However, there is limited evidence on the application of mHealth interventions and incentives during the phase when one is being presumed for TB and on how they can improve completion of the diagnostic process.

Uganda’s TB burden has persisted over the years, and the country is still ranked among the 30 countries in Africa with a high burden of both TB and HIV, with an incidence of 198 cases per 100,000 population [1]. Recent studies from Uganda have reported prediagnosis LTFU of up to 40% [20] and pretreatment LTFU of 19% [21]. Diagnosis and initiation of TB treatment are critical for controlling TB transmission and achieving good patient outcomes, particularly when medication adherence is maintained [2]. Therefore, this situation calls for bold actions and innovations to reduce the number of patients lost to follow-up before completing TB diagnosis (prediagnosis LTFU) and those lost to follow-up before initiating treatment when diagnosed (pretreatment LTFU). In Uganda, mHealth interventions have emerged as promising tools to enhance TB care by improving patient outcomes and health care processes. These mHealth interventions have been used to address challenges in TB care, including contact investigation, delivery of test results, adherence to appointments, linkage to care, and treatment adherence [6,22].

The consequences of prediagnosis and pretreatment LTFU are serious. Patients with untreated TB remain infectious and can transmit TB to others, while failure to initiate treatment contributes to increased morbidity and mortality [23-26]. Therefore, monitoring the outcomes of persons with presumed TB is an important aspect of TB control [5]. This study will thus assess the effect of SMS reminders, telephone calls, and transport incentives on enhancing completion of TB diagnosis and initiation of treatment in Uganda. Assessing the effect of these interventions will provide evidence on whether reminding patients using SMS reminders or telephone calls, with or without conditional cash incentives, can enhance completion of TB diagnosis and initiation of treatment for improved patient outcomes and hence aid in designing targeted interventions and policies.

### Goal of the Study

This randomized controlled trial aims to assess the effect of SMS reminders, telephone calls, and transport incentives sent to persons with presumed TB and those with confirmed TB on enhancing completion of TB diagnosis and initiation of treatment for diagnosed patients. The TB care continuum comprises 4 steps: screening, diagnosis, treatment initiation, and treatment completion [3,4]. This study will address LTFU along the TB care continuum at 2 time points: before diagnosis and before treatment*.* Prediagnosis LTFU refers to the failure to test for TB and obtain results within 30 days from the date of being presumed. Pretreatment LTFU refers to failure to initiate treatment after TB has been confirmed. The proposed intervention will use SMS reminders and telephone calls to improve communication between patients and health care providers, while the transport incentives will help address the economic barriers to diagnosis completion and treatment initiation.

### Objectives and Hypothesis

The primary objective is to assess the effect of SMS reminders, telephone calls, and transport incentives on completion of TB diagnosis among persons with presumed TB and initiation of treatment for diagnosed patients. The secondary objectives are to determine the median turnaround time for TB diagnosis and treatment initiation and to examine the acceptability and feasibility of the interventions. We hypothesize that compared to standard of care (SOC), each individual intervention—SMS reminders alone or telephone calls alone—will improve completion of TB diagnosis and initiation of treatment by reducing prediagnosis LTFU by a minimum of 40% (from 24% to 14.4%), while a combined intervention—SMS reminders or telephone calls coupled with transport incentives—will reduce prediagnosis LTFU by 50% (from 24% to 12%). This protocol follows the SPIRIT (Standard Protocol Items: Recommendations for Interventional Trials) reporting guidelines [27].

## Methods

### Study Setting

The study will be conducted in 6 government health facilities in central Uganda: Kiruddu National Referral Hospital, Entebbe Regional Referral Hospital, Mukono General Hospital, Luwero General Hospital, Kawolo General Hospital, and Wakiso Health Center (HC) IV (a lower-level facility). The selection of these health facilities ensures a mix of urban and rural settings and different administrative levels to increase the generalizability of the findings. Uganda’s government health system consists of national referral hospitals, regional referral hospitals, and the district health system [28]. The district health system is further divided into district general hospitals; HCs IV, III, and II; and village health teams [28,29]. National referral hospitals provide comprehensive specialist services, while regional referral hospitals have specialists in only some specific fields. District general hospitals and HC IVs have physicians. HCs are graded based on the administrative zone served, population size, and services offered. HC IVs serve a county or municipality with a population of approximately 100,000 people and provide emergency surgery, blood transfusion, and all general medical services offered at lower-level health facilities. HC IIIs serve a subcounty with a population of approximately 20,000 people and provide maternity, inpatient, and laboratory services in addition to all health services offered at an HC II. HC IIs provide health services to a parish, ward, or division with a population of approximately 5000 people and offer outpatient care, prenatal care, immunization, and community outreach services [29].

In the study facilities, patients presenting with symptoms suggestive of TB (eg, cough, fever, weight loss, and night sweats) are identified and their demographic, contact, and clinical details recorded in the registers for persons with presumed TB at the different facility entry points. Patients are evaluated for TB using Xpert MTB/RIF, urine lipoarabinomannan, or chest X-ray depending on their symptoms, with diagnosis primarily conducted via Xpert MTB/RIF as recommended by the Ministry of Health [30]. Persons with presumed TB are offered sputum testing using Xpert MTB/RIF or sputum smear microscopy, while those unable to produce sputum are offered alternative diagnostic tests (eg, chest X-ray, urine lipoarabinomannan, sonography, tissue biopsy, and cerebrospinal fluid analysis). Details of patients who complete the required investigations are subsequently recorded in the laboratory or radiology registers. Thereafter, patients confirmed to have TB are started on treatment and recorded in the unit TB register (Figure 1). Ideally, the results of Xpert MTB/RIF tests should be available within 2 hours, allowing persons with presumed TB to receive their results on the same day as sputum submission. However, challenges such as high patient loads, cartridge shortages, lack of on-site Xpert MTB/RIF equipment, and low staffing levels in laboratories, among others, often prevent same-day completion of the diagnostic process, contributing to a considerable proportion of patients being lost to follow-up [31-33].

**Figure 1. F1:**
[figure not shown]
Patient flow through the study facilities. LTFU: loss to follow-up; TB: tuberculosis.

### Trial Design, Population, and Eligibility

This will be a multicenter individual randomized controlled trial with five arms: (1) SOC (control arm), (2) SMS reminders only, (3) telephone calls only, (4) SMS reminders and a transport incentive, and (5) telephone calls and a transport incentive. This intervention was designed and adapted through stakeholder engagements in a co-design workshop. The original design included SMS reminders only and a transport incentive [34]. However, based on stakeholder engagements, telephone calls were added to address the following concerns: (1) the risk of unintentional disclosure if someone other than the recipient reads the SMS text message; (2) existing SMS fatigue due to high volume of messages from telecom companies, leading to a likelihood of messages being ignored or deleted; (3) lack of real-time 2-way communication; and (4) lack of usefulness for patients who cannot read. Telephone calls were preferred because they offer privacy and foster 2-way communication in real time .

### Description of the Study Arms

#### SOC Arm (Control)

Patients in the SOC arm (control) will continue to receive routine TB care, according to the Uganda Ministry of Health guidelines, including (1) screening individuals for TB, (2) identifying persons with presumed TB and recording their details in the TB register, (3) referring for testing, (4) receiving results, (5) irregular automated SMS text notification from the Xpert MTB/RIF machine to attending clinicians when results from the tests are ready, (6) irregular telephone calls to patients with positive TB test results to return to the health facility and start treatment, and (7) initiating treatment for patients with confirmed TB. There are irregularities in sending of SMS and making telephone calls due to inconsistencies in availability of funds, breakdown in the Xpert MTB/RIF server system, and limited human resource to support these processes.

**Intervention Arms**

The intervention will comprise 3 enhanced approaches to motivate participants to complete TB diagnosis: SMS reminders, telephone calls, and transport incentives. These interventions will be delivered in four arms: (1) SMS reminders only, (2) telephone calls only, (3) SMS reminders and a transport incentive, and (4) telephone calls and (5) a transport incentive.

#### SMS Reminders Only

Participants in this arm will receive up to 3 SMS reminders. The first reminder will be sent on day 0, the day of study enrollment. The second reminder will be sent once the patient’s results are ready. If the patient does not return to complete the TB diagnostic process (ie, testing and receiving results) within 1 day of the second reminder, a third reminder will be sent. This third reminder will serve as a reinforcement, reminding participants to return and complete diagnosis or initiate treatment if they have not already done so. Standardized SMS reminders will be manually sent by the research team through the telecom service providers MTN and Airtel in either Luganda (the local language) or English, based on the participant’s language preference determined at enrollment. The SMS reminders are planned to be 1-way (unidirectional) and the content neutral, excluding any mention of the word “TB” or the patient’s name. The specific wording of the SMS reminders will be co-designed with stakeholders including persons with presumed TB and health workers. Quality control officers will verify the SMS reminders sent daily, checking for the correctness of recipient telephone numbers and ensuring that all reminders are sent on time as per the study procedures. Each day, quality control officers will randomly select at least 4 participants from the SMS reminder arm or from among those scheduled to receive the second or third reminder and cross-check their details on the study telephone to confirm that the participant received the appropriate SMS reminder and in the preferred language. They will also cross-check the correctness of the telephone number that received the SMS reminder vis-à-vis the one recorded in the register for persons with presumed TB. Successful transmission of reminders will be checked by requesting sample statements from the telecom companies to confirm SMS dispatch to patients. Moreover, at follow-up, participants will be asked whether they received either an SMS reminder or a telephone call and a transport incentive, further corroborating whether the participant received the SMS reminder.

#### Telephone Calls Only

In this arm, participants will receive up to 3 telephone calls as reminders, in addition to the usual SOC. The first telephone call will be made on the day of enrollment (day 0). The second telephone call will be made once the patient’s results are ready. If the patient does not return to complete the TB diagnostic process within 1 day of the second call, a third telephone call will be made. The third telephone call will serve as a reinforcement, reminding participants to return and complete diagnosis or initiate treatment if they have not already done so. Telephone calls will be made in either Luganda (the local language) or English, based on the participant’s language preference determined at enrollment.

Daily quality checks will be carried out to ensure delivery of the intervention to participants. At least 4 participants from the telephone call arm or from among those scheduled to receive the second or third telephone call will be randomly selected for the quality checks. Participant details will be cross-checked on the study telephone by the quality control officers at each study site to confirm that the participant received the appropriate telephone call. Call logs will also be checked to confirm the language used in the telephone call vis-à-vis the participant’s preferred language and the correctness of the telephone number that received the call. Research assistants will continue attempting telephone calls if a patient does not answer the telephone, if another person answers, if it is not convenient for a patient to talk, or if the telephone is switched off until an effective call is made to the intended participant. A successful call will be defined as one in which a patient is reached, and a conversation takes place.

#### SMS Reminders and a Transport Incentive

Participants in this arm will receive the same SMS reminder package as those in the SMS reminder–only arm, along with a transport incentive of UGX 10,000 (approximately US $3). This transport incentive will be provided either after submitting a sputum sample in case the participant was unable to produce the sputum on the first day of the health facility visit or upon receiving their test results. The transport incentive will be disbursed through a prepaid mobile money system to ensure accountability for both the patient and the study team and to comply with the ongoing government campaign promoting the use of electronic cash [35]. These interventions will be administered in addition to the SOC provided at the health facility.

#### Telephone Calls and a Transport Incentive

The same telephone call package received by participants in the telephone call–only arm will be offered to those in this arm, along with a transport incentive of UGX 10,000 (approximately US$ 3). This will be in addition to the SOC received at the health facility. This transport incentive will be provided either after submitting a sputum sample in case a participant was unable to produce sputum on the first day of the hospital visit or upon receiving their test results. We will use the prepaid mobile money system to pay the transport incentive to participants in this study arm.

### Sample Size Estimation

An estimated sample size of 2389 participants was determined to achieve 80% power at a type I error of 5%, adjusted for multiple comparisons using the Bonferroni correction. Four comparisons were considered according to the study objectives; therefore, the adjusted level of significance is 1.25%, with a corresponding 2-tailed Z value of 2.238. We also adjusted for a 24% LTFU among patients with TB, based on findings from the formative study that informed the design of these interventions. We assumed a 40% reduction in LTFU based on previous similar studies [36,37] for comparisons between SOC and either SMS reminders alone or telephone calls alone, resulting in an assumed proportion of LTFU of 14.4% in both these groups. For comparisons between SOC and combined interventions (SMS reminders or telephone calls with a transport incentive), a 50% reduction will be considered clinically significant, given the expected higher impact of the incentive. The sample size has been further adjusted for clustering using a design effect of 1.5 to account for the clustering anticipated at the health facility level and a postenrollment attrition rate of 20%.

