### Randomization and Blinding

Eligible participants will be randomly assigned by research assistants to 1 of the 5 study arms using permuted block randomization in a ratio of 2:2:2:1:1 via a predesigned mobile app (Figure 2). The block sizes will be varied to minimize predictability. A computer algorithm will be designed by the biostatistician together with the app designer to generate the allocation sequence in blocks of 8 and 16, assigning their order randomly. The allocation sequence will then be input into the predesigned mobile app for automatic randomization once the research assistants input the participant’s unique study ID number. Due to the nature of the interventions, participants will not be blinded to their assigned study arm. Research assistants will also not be blinded, given their role in delivering the interventions. However, the outcome assessors and data analyst will remain blinded to the study arms.

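### Once the four comparisons with SOC are tied to a 5% family-wise error, Holm's step-down would recover power that single-step Bonferroni at 1.25% gives up, at no cost in participants

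*Protocol article*

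**What the plan says.** In the protocol article, Sample Size Estimation gives the target as "80% power at a type I error of 5%, adjusted for multiple comparisons using the Bonferroni correction". It then sets the level for each comparison: "Four comparisons were considered according to the study objectives; therefore, the adjusted level of significance is 1.25"%, "with a corresponding 2-tailed Z value of 2.238".

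The planning rates of loss to follow-up (LTFU) are 24% under standard of care (SOC), 14.4% for SMS alone and for calls alone, and 12% for either mode with a transport incentive. Objectives and Hypothesis expects every intervention arm to beat SOC; of the combined arms it says that they "will reduce prediagnosis LTFU by 50% (from 24% to 12"%.

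The overview under Data Management and Analysis does not mention the four comparisons or the 1.25% level. It gives a single .05 threshold. No stepwise procedure is named anywhere.

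**The concern.** The only multiplicity method in the article holds each of the four comparisons to 1.25%, whatever happens to the other three. Holm's procedure starts at the same 1.25% but relaxes the level after each success. It controls the same 5% family-wise error under any dependence, including the dependence created by the shared SOC arm, and it rejects everything that Bonferroni rejects.

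The protocol hypothesises that all four interventions work. That is the situation in which a fixed 1.25% costs most, because after the first success the remaining tests need not be held so strictly. What is at stake is missing real effects of the planned size with no gain in error control.

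**Working it through.** **Inputs.** From Sample Size Estimation: N = 2389, 80% power, four comparisons, 20% attrition, a design effect of 1.5, and LTFU of 24% (SOC) and 14.4% (single-mode arms). From Objectives and Hypothesis: 12% (incentive arms). From Randomization and Blinding: allocation 2:2:2:1:1, so SOC and each single-mode arm hold 2/8 of participants and each incentive arm 1/8.

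**1. Reproduce 2389.** Pooled two-proportion formula, 24% against 14.4%, mean 0.192, with the stated Z of 2.238:

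n = [2.238·√(2·0.192·0.808) + 0.8416·√(0.24·0.76 + 0.144·0.856)]² / 0.096² = (1.2466 + 0.4653)² / 0.009216 ≈ 318 per double-size arm.

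N = 318 × 4 × 1.5 / 0.8 = 2385, within 0.2% of 2389. The target is therefore reproduced with the Z that the article prints. That Z has a two-tailed area of 2.52%; the two-tailed 1.25% value is 2.498, which gives n = 375 and N = 2813. This is a separate problem and matters here only for the starting level of power.

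**2. Effective sample.** 2389 × 0.8 / 1.5 = 1274, that is about 318.5 in SOC and in each single-mode arm, and 159 in each incentive arm.

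**3. Single-step power at a true two-sided 1.25%.** Power = Φ[(difference − 2.498·SE₀)/SE₁], where SE₀ is the pooled and SE₁ the unpooled standard error.
- Single-mode arm: (0.096 − 2.498 × 0.03121)/0.03098 = 0.582, power 72.0%.
- Incentive arm: (0.12 − 2.498 × 0.03882)/0.03515 = 0.655, power 74.4%.

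**4. Holm against Bonferroni.** Simulation of binomial outcomes in five arms of 319/319/319/159/159, with a shared SOC arm, pooled z tests and all four planned effects real:

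| | Bonferroni | Holm |
|---|---|---|
| Single-mode arm | 72% | 82% |
| Incentive arm | 75% | 84% |
| All four shown | 44% | 67% |
| At least one shown | 96% | 96% |
| Family-wise error, no effects | 4.5% | 4.5% |

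A normal approximation gives slightly lower Holm power: 80.7% and 83.0%, gains of 8.8 and 8.6 points.

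**5. How the gain depends on assumptions.**
- Three real effects: about 5 points (a single-mode arm reaches about 78%).
- Two real effects: about 2 points.
- One real effect: about 0.
- All four real, attrition but no design effect: 4 to 5 points (about 90% to 95%, and 92% to 96–97%).
- All four real, at the protocol's own Z of about 2.24: about 8 points (80.0% to 88.2%, and 82.6% to 90.2%).

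**6. Conflict with intervals.** Any rejection that Holm adds has P above .0125, so a 98.75% interval matching the test includes no effect. In the planning case about 30% of simulated trials have at least one such rejection.

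**The case against.** The strongest reply is that Bonferroni appears only in the sample size section. Sizing a trial on Bonferroni does not oblige the analysis to test that way, and the choice of procedure can be left to an analysis plan that is not shown. This stands in part: the article does not say that the final tests will be single-step at 1.25%. But the article does name a method for its four comparisons and also prints a .05 threshold that does not match it. One sentence must settle this in any case, and the choice of procedure belongs in it.

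Second, the baseline matters. Against the .05 threshold as printed, single-comparison power is about 87% and 89%, so Holm is stricter and not a gain. This stands. The advantage exists only relative to Bonferroni, once the family-wise 5% is kept.

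Third, a reader might infer that about 9 points are lost on every comparison in any event, or that Holm restores the stated 80%. The documents support neither. The 9 points require all four effects at their planned size and the full design effect. The 72% start comes from the Z value; at the printed Z, single-step power is already 80.0% and 82.6%. With one ineffective arm, a single-mode arm stays at about 78% under Holm.

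Fourth, tests and intervals would no longer agree, and every decision that Holm adds is such a case. This is a real price and must be disclosed.

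Finally, 2355 of 2389 participants had been recruited by late August 2025, an interim analysis is planned and preliminary analyses are reported as ongoing. A move to a less strict rule therefore needs care over timing.

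**Conclusion.** The point holds as one of efficiency. Bonferroni over four comparisons is valid and controls the 5% error; a reader might take this point to mean that the protocol's error control is wrong, and it is not. If the analysis is tied to the family-wise 5%, Holm is never less powerful. In the protocol's own planning case it adds about 9 points per comparison and raises the chance of showing all four effects from 44% to 67%.

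These figures rest on all four effects being real at 14.4% and 12% against 24%, on 20% attrition and a design effect of 1.5, and on a true two-sided 1.25%. With fewer real effects or less clustering the gain is smaller, down to nothing with a single effective arm. The change is worth making, but it does not replace correction of the Z value.

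**What to change.** State in the analysis section, by dated amendment and before any between-arm results are seen, that the four two-sided P values against SOC are ordered from smallest to largest and compared with .0125, .0167, .025 and .05, stopping at the first failure. For these comparisons this replaces both the fixed 1.25% and the unadjusted .05.

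Report Holm-adjusted P values as the basis for decisions. If 98.75% intervals are kept, say that they are not the decision rule and may include no effect where Holm rejects. Restate power with the condition that all four effects are real, and give the figures for fewer real effects beside it.

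The change needs no participants and no new data, and it works with whichever regression model supplies the P values. Its costs are the amendment, a record that between-arm results had not been seen, and the loss of agreement between tests and intervals.

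### The sample size uses the 1-tailed Z for a 1.25% level but calls it 2-tailed; on the plan's own assumptions 2389 participants give about 72% power, not 80%, for each single-intervention comparison

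*Protocol article*

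**What the plan says.** The Sample Size Estimation section of the protocol article gives a total of 2389, "determined to achieve 80% power at a type I error of 5%, adjusted for multiple comparisons using the Bonferroni correction". It bases the correction on four tests ("Four comparisons were considered according to the study objectives") and then writes: "therefore, the adjusted level of significance is 1.25%, with a corresponding 2-tailed Z value of 2.238".

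The planned effects, given there and under Objectives and Hypothesis, are a fall in prediagnosis loss to follow-up (LTFU) from 24% to 14.4% for SMS alone or calls alone, and from 24% to 12% for either one with a transport incentive. The total is inflated by a design effect of 1.5 and for 20% attrition. Randomization and Blinding sets the allocation: "using permuted block randomization in a ratio of 2:2:2:1:1".

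**The concern.** A critical value and a significance level determine each other once the number of tails is fixed. The value 2.238 does not belong to a 2-tailed test at 1.25%; it belongs to a 1-tailed test at that level or, equivalently, a 2-tailed test at about 2.5%.

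If this were only a slip in reporting, the sample size would still be right. If the value was used in the formula, the Bonferroni adjustment was applied at half strength in the sizing, and the trial is smaller than its stated power requires. A null result for SMS alone or calls alone would then be read against a type II error of 20% when, on the plan's own assumptions, it is about 28%.

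**Working it through.** **1. The critical value**

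- Two-sided 1.25%: z(1 − 0.0125/2) = 2.498
- One-sided 1.25%: z(1 − 0.0125) = 2.241
- The stated 2.238: upper-tail area 0.0126, two-tail area 0.0252

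To rounding, 2.238 is the one-sided value.

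**2. Reproducing 2389**

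Inputs: p1 = 0.24 and p2 = 0.144 (Objectives and Hypothesis; Sample Size Estimation); 80% power, so zβ = 0.842; design effect 1.5; attrition 20%; allocation 2:2:2:1:1. The ratio has 8 units and a full-size arm has 2, so the total is 4 full-size arms. The article does not name its variance form; the pooled two-proportion formula without continuity correction is the one that fits:

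n per arm = [zα·√(2p̄(1 − p̄)) + zβ·√(p1(1 − p1) + p2(1 − p2))]² / (p1 − p2)²

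Here p̄ = 0.192, the first root is 0.5570, the second is 0.5529, and p1 − p2 = 0.096. Total = n × 1.5 / 0.8 × 4.

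| zα | n per arm | after × 1.5 / 0.8 | total |
|---|---|---|---|
| 2.238 | 318.0 | 596.2 | 2385 |
| 2.2414 | 318.7 | 597.6 | 2390 |
| 2.4977 | 374.0 | 701.3 | 2805 |

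The stated 2389 lies between the first two rows and is about 15% below the third. The one-sided value was therefore used in the calculation. Some variants with 2.498 come within 3% of 2389, but only by dropping the attrition adjustment, or by sizing on 24% versus 12% alone with attrition as × 1.2 and a continuity correction. Neither fits the method described.

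**3. Power at 2389 with the correct value**

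Effective size of a full arm: 2389/4 × 0.8 / 1.5 = 318.5. Each combined arm has half that, 159.3.

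Power = Φ[(p1 − p2 − 2.498·SE0) / SE1], where SE0 is the standard error under the null and SE1 under the alternative.

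- Single intervention, 24% versus 14.4%, pooled: SE0 = 0.03121, SE1 = 0.03098, so Φ[(0.096 − 0.07795)/0.03098] = Φ(0.583) = **72.0%**. Unpooled (SE0 = SE1): 72.6%.
- Combined intervention, 24% versus 12%, 318.5 versus 159.3, pooled: SE0 = 0.03882, SE1 = 0.03515, so Φ[(0.12 − 0.09696)/0.03515] = Φ(0.655) = **74.4%**. Unpooled: 82.0%.

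As a check, the same calculation with 2.238 returns 80.1% for the single-intervention comparison, which is the claimed power.

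**4. Reduction detectable with 80% power at 2389, two-sided 1.25%**

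- Single arms, pooled: 24% to 13.7% (13.68; 10.32/24 = 43% reduction, against the planned 40%).
- Combined arms, pooled: 24% to 11.4% (11.42; 12.58/24 = 52% reduction, against the planned 50%). Unpooled: 24% to 12.2%.

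**5. If 2.238 were instead kept as the test threshold**

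The Bonferroni bound would be 4 × 2.52% = 10.1%. Simulating the four correlated comparisons with the shared control arm gives a family-wise error of about 8.7%, against about 4.5% with 2.498.

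**The case against.** The strongest reply accepts the mislabel and disputes its consequence.

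- **Scope.** The 72% covers two of the four comparisons. For the combined arms, power falls below 80% only with pooled variance, and the article does not name its formula. This stands as a limit on the claim. The pooled form is, however, the one that reproduces 2389, and it corresponds to the planned chi-square test.
- **Inflation factors.** With individual randomisation, facility clustering may cost less than a design effect of 1.5. The primary outcome is also defined over everyone recruited and analysed by intention to treat, so the full 20% may not be lost. With 2.498, single-intervention power would be 81% at a design effect of 1.25, 83% with 1.5 and no attrition loss, and 90% with no design effect and 20% attrition. So 72% is what the planning assumptions imply, not a fixed property of the trial. That does not rescue the calculation as stated, because the article adopts both factors. Reading attrition as × 1.2 still gives only about 74% to 75%.
- **Error rate.** No section makes 2.238 a test threshold; Data Management and Analysis uses P < .05, at which single-intervention power would be about 87%. The 8.7% is therefore hypothetical. But an unadjusted .05 does not deliver the Bonferroni-controlled error that the sample size claims either.
- **Timing.** With 2355 recruited by August 28, 2025, the size can hardly change. That is true, and the correction does not need it to.

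A one-sided intention is not a way out: the text says 2-tailed, and nothing in the article states a one-sided test.

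**Conclusion.** The plan is wrong as written. That 2.238 is not the 2-tailed value at 1.25% needs no assumption. That it set the sample size rests on an inferred formula which comes within 0.2% of 2389.

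Under the plan's own event rates, design effect, attrition and allocation, the shortfall is about 8 percentage points for each single-intervention comparison, whichever variance form is used. For the combined arms it is about 6 points with pooled variance and none with unpooled. Reaching 80% for the single-intervention comparisons would have needed about 2805 participants, some 416 more than 2389. The claims of 80% power and a Bonferroni-controlled 5% error cannot both hold at 2389 for those comparisons.

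**What to change.** In Sample Size Estimation, replace 2.238 with 2.498 as the 2-tailed value at 1.25%, and name the variance formula. Then do one of the following:

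- Restate power at 2389 under the design effect of 1.5 and 20% attrition: about 72% for SMS alone or calls alone, and about 74% for each combined arm (pooled; 82% if unpooled variance is adopted).
- Keep 80% power and state the detectable effects: LTFU from 24% to 13.7% for the single arms and from 24% to 11.4% for the combined arms (pooled).

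The change is wording only. No participants, endpoints or tests change; the cost is a less favourable stated power. It should be made before results are reported, so that the restatement is clearly independent of the data.
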